#### Secondary outcomes

##### Severity of depression and anxiety

The Patient Health Questionnaire (PHQ) is a self-administered version of the PRIME-MD diagnostic instrument for common mental disorders [47]. The PHQ-9 is the depression module, which scores each of the nine DSM-IV criteria from 0 (not at all) to 3 (nearly every day). It is used to monitor the severity of depression and response to treatment. The Generalized Anxiety Disorder Scale (GAD-7) is a diagnostic self-report scale for screening, diagnosis, and severity assessment of anxiety disorders [48]. The GAD-7 is based on seven items, which are scored from 0 (not at all) to 3 (nearly every day). Both PHQ and GAD-7 have been recommended by the International Consortium for Health Outcome Measurement (ICHOM; [49]).

In line with recommendations by ICHOM [49] for personality disorders, and for depressive and anxiety disorders, the Columbia Suicide Severity Rating Scale (C-SSRS; [50]) will be used to assess suicidal thoughts and behaviours. The screener version of the scale assesses whether adolescents meet the criteria for specific forms of suicidal behaviour and consists of 3–6 ‘yes/no’ questions (the number of questions depends on the answers given).

To compare the results of this trial with those of other MBT trials, the Brief Symptom Inventory (BSI; [51]) and the Child Behavior Checklist (CBCL; [52]) are also included. The BSI is a self-report questionnaire that also covers depression and anxiety dimensions and can also be used as a global severity index. Adolescents score each item on a 5-point scale ranging from 0 (not at all) to 4 (extremely). Scores represent the intensity of distress over the past week. The Dutch version of the BSI has a good reliability (Cronbach’s *α* ranging from 0.71 to 0.88, test–retest reliability ranging from *r* = 0.71 to 0.89) [51]. The CBCL is a child behaviour questionnaire completed by parents. It assesses the competences and emotional and behavioural problems (e.g. depression and anxiety) of the adolescent in a standardized format. The scores on the different domains indicate possible problem areas for the adolescent, from a parental perspective [52].

##### Personality functioning

Improvement of personality functioning will be assessed by the Level of Personality Functioning Scale – Brief Form, version 2.0 (LPFS-BF 2.0; [53]), as a secondary outcome. This self-report measure consists of 12 items rated on a 4-point Likert scale ranging from 0 (very false or often false) to 3 (very true or often true), reflecting the 12 facets of the LPFS as described in section III of the DSM-5 [54]. The internal consistency of the LPFS-BF 2.0 is satisfactory, and sensitivity to change is high [53]. The LPFS-BF 2.0 fits into the recent tradition of dimensional measures of personality problems and has been recommended by ICHOM [49].

Related to improvements in personality functioning are improvements in mentalizing abilities. The Reflective Functioning Questionnaire (RFQ; [55]) is a brief self-report screening measure of reflective functioning. It consists of eight items (e.g. ‘People’s thoughts are a mystery to me’), which are scored on a 7-point Likert scale ranging from 1 (completely disagree) to 7 (completely agree). This instrument assesses the level of certainty (RFQc) and uncertainty (RFQu) about mental states. Internal consistency of RFQc and RFQu respectively are *α* = 0.65 and *α* = 0.77 in a clinical sample and *α* = 0.67 and *α* = 0.63 in a non-clinical sample, respectively [55].

##### Social functioning

The World Health Organization Disability Assessment Scale (WHODAS 2.0) assesses disability in psychiatric populations [56]. The 12-item version assesses impairment in six domains: mobility, self-care, understanding and communication, interpersonal relationships, life activities, and community participation. The WHODAS 2.0 has also been recommended by the ICHOM [49].

The adolescents’ quality of life will also be assessed as a measure of social functioning. The KIDSCREEN-10 is an international cross-culturally comparable quality-of-life assessment instrument validated for children and adolescents between 8 and 18 years. It consists of ten items, which provide a global measure of health-related quality of life [57]. The KIDSCREEN-10 has also been recommended by the ICHOM [49]. The EQ-5D-5L is a self-report questionnaire comprising five dimensions for measuring health-related quality of life: mobility, self-care, usual activities, pain/discomfort, and anxiety/depression. Each dimension is divided into five levels (no problems, slight problems, moderate problems, severe problems, and unable to/extreme problems). The adult version of the EQ-5D-5L will be used to consistently assess the quality of life during the study, as the youth version of this questionnaire was designed to be used in adolescents up to age 15 years [58].

To assess how social relationships improve, the Dutch translation of the Network of Relationships Inventory-Behavioural Systems Version (NRI-BSV; [59]) is used. Adolescents answer 24 items regarding their relationships with important people in their social network on a 5-point Likert scale (1 = little or none; 5 = the most), which assess support and conflict in social relationships. The NRI-BSV will also be administered to parents to include their assessment of changes in the parent–child relationship.

##### Academic functioning

To assess academic functioning, adolescents will answer questions concerning their school attendance in the past month (e.g. ‘Have you been to school in the past month?’, ‘Why did you not go to school in the past month?’, ‘Did you skip classes in the past month?’), taking school holidays into account.

##### Economic evaluation

The intervention costs of MBT-early and CBT will be calculated using a mixture of bottom-up and top-down approaches and will include personnel costs, implementation costs (e.g. hosting and coaching), and overhead costs associated with the treatment (e.g. facilities for coaches).

An adapted version of the Trimbos/iMTA questionnaire for Costs associated with psychiatric illness (TiC-P; [60, 61]) will be used to calculate medical costs beyond the intervention costs specific to MBT-early and CBT. We will use the parent-form questionnaire (TiC-P Kinderen, in Dutch) to assess health care utilization at baseline, end of treatment, and at 12-, 18-, and 24-month follow-up. We slightly adapted the questionnaire by adding questions about the frequency and duration of (suicidal) crisis (with hospitalization needed) and removing questions that are not related to the problems of the target population (e.g. ‘How many appointments did your child have with a dietician in the past 3 months’).

In line with the iMTA Valuation of Informal Care Questionnaire [62], additional costs of parents that are needed for the treatment of their child will be assessed separately (e.g. taking leave from work to bring their child to therapy, transportation costs, having less leisure time). Parents will answer questions concerning this invested time (e.g. ‘Did you take leave from work for your children’s therapy at “Mentaal Beter/GGz Breburg/de Viersprong” in the past 4 weeks?’ or ‘Did you make any extra costs because your child had therapy in the past 4 weeks? E.g. extra travel expenses or arranging a babysitter’). These questions will be assessed at the end of treatment and at 12-, 18-, and 24-month follow-up. QALYs will be estimated by calculating the area under the EuroQol EQ-5D/time curve [63].

##### Demographic variables

At the initial assessment (prior to randomization), adolescents will answer questions regarding demographic variables including their living situation, nationality, level of education, and their current school status, employment, or both.

### Participant timeline {13}

Figure 1 shows the participant timeline.

**Fig. 1 Fig1:**
[figure not shown]
Consolidated Standards of Reporting Trials (CONSORT) flow chart

### Sample size {14}

The sample size is determined by the predicted difference between the groups on the primary outcome, the BPDSI-IV-ado [46]. Consistent with previous studies on MBT for adolescents [43, 64] and MBT for adolescents compared with treatment as usual [27], we expect a medium effect size (Cohen’s *d* = 0.50) difference between MBT-early and CBT. Based on the BPDSI-IV-ado and with a two-sided *α* = 0.05, a power of 0.80 and a correlation of 0.50 between the repeated measures, based on Bales et al. [65] and Hutsebaut et al. [43], we require 59 participants in each treatment group (118 in total) with at least 1 follow-up measurement. Because of the vulnerable and unpredictable target population, we anticipate a 10% attrition rate and therefore intend to recruit at least 66 participants per group.

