Despite this need for appropriate strategies for early intervention to reduce the short-term burden and prevent long-term disabilities, several studies suggest that current mental health services often do not provide an appropriate response to the health needs of these young persons. Data from the Netherlands [14] as well as Australia [15] show that young persons with BPD remain largely undetected in primary services, are not referred to appropriate treatment, and are rarely provided appropriate, evidence-based treatments. Brief psychosocial treatments that are common in primary care seem to be less effective for young people with BPD. For example, in a prospective follow-up study of young people receiving cognitive behavioural therapy (CBT) for depression, the subgroup of females with both depressive problems and BPD showed poor distal outcomes. These young people, compared to those without BPD, had up to four times higher likelihood of experiencing recurrent depressive episodes [16]. The limited effects of brief treatments for these young people seem to be in large part due to the considerable dropout rate from these treatments. Approximately 40–50% of young people with BPD drop out from treatment prematurely, even though they experience high levels of distress and suffering [17]. This suggests that these treatment approaches may not be adequately tailored to the specific needs and problems of young people with emerging BPD. In addition, current services are primarily organized based on a ‘stepped-care’ strategy; initiating care for these young people with brief and generic interventions which are subsequently upscaled in the case of poor response. Yet, poor or non-response in these young people is the rule rather than the exception. In a study on primary care in Australia for 12- to 25-year-olds, for instance, patients with BPD symptoms showed no progress or deteriorated in terms of social and occupational functioning (45%), psychological stress (60%), and quality of life (69%) [15]. Importantly, aside from the lack of efficiency in attaining, this approach generated iatrogenic damage in these youngsters as failed treatment attempts lead to disappointment in and distrust of mental health services [18], which may undermine future care-seeking or treatment success.

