In response to the need for appropriate and in-time treatments, and the lack of evidence of treatment programmes for young people with BPD, the past decades have witnessed the development and evaluation of a range of treatment programmes for young people with BPD features, based on adaptations of treatments for BPD in adults. These include dialectical behaviour therapy (DBT-A) [19], mentalization-based treatment (MBT-A) [20], and transference-focused psychotherapy [21]. The evidence base for these adaptations is rather scarce. A recent review identified only ten randomized clinical trials [22–31]. The results indicate that the majority of these trials did not show the superiority of the specialized treatments compared with treatment as usual. Dropout rates varied widely, ranging from 15 to 75%. Moreover, the heterogeneity of the samples involved in these studies is typically large [17, 22]. Compared with treatments for adults with BPD, the majority of psychosocial treatments for young people with BPD were relatively brief (e.g. HYPE, consisting of sixteen sessions [23]) or were characterized by low treatment intensity (e.g. DBT-A, involving weekly sessions [26]). This matches a clinical staging perspective, with increasing consensus that such interventions, whether brief or low-intensity, may be best suited for addressing the early stages of BPD, characterized by low to moderate risk profiles [32]. However, these interventions are likely to be insufficient for young people with BPD at a later stage of development. A clinical staging approach may enable better matching of treatment to the clinical needs of these young people [10, 33]. Staged care has been introduced as an alternative to stepped care [34]. The advantages of such an approach are clear. Staged care does not require individuals to fail prior treatment to be assigned to more specialist services and it enables to match the type and level of care to the clinical needs associated with the stage of illness, also minimizing the probably of early dropout and dissatisfaction with and disbelief in mental health treatments.

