## Statistical methods

### Statistical methods for primary and secondary outcomes {20a}

Data analysis will be conducted using SPSS Statistics. Treatment outcomes of the primary outcome, severity of BPD symptoms, over time will be examined using multilevel modelling. Multilevel modelling is able to model data from different time points, correcting for the dependency of observations by adding a within-subject correlation structure to the regression model. Another advantage of multilevel modelling is that it is able to handle missing data, by using the available data irrespective of the number of repeated measurements. In other words, adolescents with an incomplete number of follow-up measurements are also included in the treatment outcome analyses.

The interventions will be compared with the intention-to-treat adolescent sample, that is, with all adolescents randomized to either MBT-early or CBT.

A deviance test using restricted maximum likelihood will be used to assess whether random or fixed slopes should be assumed in models for each outcome variable. Subsequently, time will be included as appropriate (i.e. linear, logarithmic) and included in the model together with the treatment group and time by group interactions if likelihood ratio tests show significant improvement. The primary effect size of the treatments will be estimated from baseline to end of treatment and secondary effect sizes from baseline to 12-, 18-, and 24-month follow-up. Additional treatment offered in the follow-up period will be included as a covariate in the estimation of the multilevel models and effect sizes from baseline to 12-, 18-, and 24-month follow-up, as well as a predictor of treatment outcomes at 12-, 18-, and 24-month follow-up.

The secondary outcomes will be analysed similarly using multilevel modelling, in which the type of model is adapted to the outcome if needed (i.e. binary in case of the C-SSRS) from baseline to end of treatment, 12-, 18-, and 24-month follow-up. As noted, additional treatment offered in the follow-up period will be included as a covariate in the estimation of the multilevel models and effect sizes from baseline to 12-, 18-, and 24-month follow-up, as well as a predictor of treatment outcomes at 12-, 18-, and 24-month follow-up.

To examine the possible influence of missing data, we will repeat the analyses described using datasets in which missing data are imputed with state-of-the-art data imputation methods [66].

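### The 59 per group stated for 80% power does not match the primary baseline-to-end-of-treatment contrast: power at 59 is about 77% as a two-point change and about 87% if baseline-adjusted

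*Protocol article*

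**What the plan says.** The section Sample size {14} bases the calculation on the BPDSI-IV-ado. It states "we expect a medium effect size (Cohen’s *d* = 0.50) difference between MBT-early and CBT", and then, "with a two-sided *α* = 0.05, a power of 0.80 and a correlation of 0.50 between the repeated measures", that "we require 59 participants in each treatment group (118 in total) with at least 1 follow-up measurement". With 10% attrition this becomes at least 66 per group, or 132 in total. The section names no formula, no number of repeated measures and no time at which d = 0.50 is expected.

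The Primary outcome section defines the outcome as the reduction in BPD severity from baseline to end of treatment. Statistical methods {20a} agrees: "The primary effect size of the treatments will be estimated from baseline to end of treatment", with effect sizes at 12, 18 and 24 months secondary. The model there is multilevel, with time, treatment group and time-by-group terms. Time may be linear or logarithmic, and the terms are kept if likelihood ratio tests support them. Neither a baseline covariate nor a common baseline mean is mentioned. Table 1 places the BPDSI-IV-ado at baseline, end of treatment and 24 months only.

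**The concern.** A sample size should be the one required for the primary contrast under the analysis planned for it. Here the inputs and the contrast are both stated, so the figure can be recomputed, and 59 lies between the two standard answers. If the analysis compares unadjusted change, the trial is slightly short of its stated power. If it adjusts for baseline, the trial has more power than stated, and the protocol neither claims it nor secures it by specifying the adjustment.

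The unit of counting is a second mismatch. A participant with only a 24-month BPDSI satisfies the condition of at least one follow-up measurement but has no score at the time point of the primary contrast.

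**Working it through.** **Inputs (Sample size {14}):** d = 0.50 with the score SD set to 1; two-sided alpha 0.05; power 0.80; correlation rho = 0.50; 59 per group; 10% attrition. Allocation is 1:1 (Trial design {8}).

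**Step that reproduces.** 59 / 0.9 = 65.6, rounded up to 66 per group, or 132 in total. The attrition step is correct. What does not reproduce is the 59.

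**Common formula.** n per group = 2 (1.960 + 0.842)² V / d², where V is the variance of the analysed quantity relative to the score variance. (1.960 + 0.842)² is 7.849 (unrounded quantiles).

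**Two-point change comparison.**
- V = 2(1 − rho) = 2(1 − 0.50) = 1. At this correlation the change score is exactly as variable as a single score, so it makes no difference whether d is standardised by the SD of the score or of the change.
- n = 2 × 7.849 × 1 / 0.25 = 62.8, so 63 (normal). The t-based value is 63.8, so 64.
- Power at 59: 77.5% (normal), 76.8% (t).
- After 10% attrition: 63 / 0.9 = 70 and 64 / 0.9 = 71.1, so 70 to 72 per group against the stated 66.

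**Baseline-adjusted contrast** (ANCOVA, or arms constrained to a common baseline mean).
- V = 1 − rho² = 1 − 0.25 = 0.75.
- n = 2 × 7.849 × 0.75 / 0.25 = 47.1, so 48 (normal). The t-based value is 48.1, so 49.
- Power at 59: 88.0% (normal), 87.5% (t).
- The standard error relative to the change comparison is √0.75 = 0.866, a reduction of 13%.

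**Inputs that would give 59** (normal approximation, other inputs as stated). For the change comparison, d of about 0.516 or rho of about 0.53; for the baseline-adjusted contrast, rho of about 0.25. None of these is stated.

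**Other forms tried, per group:**

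| Form | n |
|---|---|
| One-sided change comparison | 50 |
| Mean of two follow-ups | 47 |
| Repeated-measures ANOVA, between-group effect, 2 measures | 49 |
| Repeated-measures ANOVA, between-group effect, 3 measures | 43 |
| Linear slope, 3 / 4 / 5 equally spaced times | 63 / 57 / 51 |
| Linear slope, visits at 0, 6 and 24 months | 58 (normal), 59 (t) |

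The last row assumes compound symmetry, an end-of-treatment visit at 6 months and d = 0.50 reached at 24 months. Moving end of treatment between 4 and 10 months gives 56 to 64 on the t basis. Under that straight line, the group difference at 6 months would be 0.50 × 6/24 = 0.125 SD, which is not a difference of 0.50 at end of treatment.

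**The case against.** The strongest reply is that the section uses longitudinal language (repeated measures, at least one follow-up) and that the planned model is multilevel with time possibly linear. The slope model above, with visits at 0, 6 and 24 months, reaches 59 on the t basis using the stated d, alpha, power and correlation. This stands as far as it goes. A reader might infer that 59 cannot be obtained from the stated inputs at all, and that is too absolute. But this route needs an end-of-treatment time that the article does not fix, and it places the 0.50 difference at 24 months. The protocol names end of treatment as primary.

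It is also fair that Statistical methods {20a} leaves the form of time open. The 77% is therefore the power of a two-point change comparison, not of every model that section allows. Likewise, a participant with only a 24-month score adds little to the end-of-treatment contrast if time is categorical, but does contribute if time is continuous.

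A further tempting reading is that 10% attrition is contradicted by the article's own background, which says "Approximately 40–50% of young people with BPD drop out from treatment prematurely" and, of earlier trials, "Dropout rates varied widely, ranging from 15 to 75" per cent. The documents do not support it. Those figures are dropout from treatment. The 10% concerns loss of assessments, and Provisions for post-trial care {30} says that treatment dropouts will still be followed unless they withdraw consent.

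Finally, the absence of baseline adjustment from a condensed article is not in itself an error. The adjustment is proposed because it resolves the mismatch at no cost in participants.

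**Conclusion.** The point holds for the primary contrast as the protocol defines it. With the stated inputs, 59 per group gives about 77% power for a two-point change from baseline to end of treatment, or about 87% with the baseline score adjusted for; neither is the stated 80%. The size is modest: 64 − 59 = 5 evaluable participants per group short in the first case (4 on the normal approximation), or 59 − 49 = 10 above requirement in the second (11 on the normal approximation). The recruitment target of 66 is worded as a minimum, which leaves room for more.

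These figures assume equal variance at the two time points, d expressed in SDs of the BPDSI score, 1:1 groups and 59 participants per group with both baseline and end-of-treatment scores. They do not show which calculation the authors used, and they do not show that the 10% loss is too low.

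**What to change.** Keep 132 participants.

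1. Specify the primary analysis as the group difference in BPDSI-IV-ado at end of treatment with baseline BPDSI adjusted for, either through a common baseline mean in the multilevel model or by ANCOVA.
2. Restate the sample size paragraph with its formula and contrast: d = 0.50, two-sided alpha 0.05 and correlation 0.50 require 49 per group for 80% power (t-based), and 59 per group give about 87%.
3. Count participants with an end-of-treatment BPDSI instead of those with at least one follow-up measurement.
4. If the unadjusted change contrast is kept, state the power at 59 per group as about 77%.

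The cost is a rewritten paragraph and one model constraint or covariate, using a baseline score that is already collected. It should be settled before outcome data are analysed. A table of power under losses above 10% is an optional sensitivity display and should be labelled as resting on assumed rates.

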### Recruitment {15}

Adolescents will be recruited at three mental healthcare institutions in the Netherlands: Mentaal Beter, GGz Breburg, and de Viersprong. These settings treat young people referred for (emerging) mental health problems and offer interventions for a wide range of mental health problems. Adolescents and their parents are informed during the admission by the clinician about participating in this study and will receive written information. The information folder also includes an infographic about the study. The research team is available to answer questions about the study and will ask for informed consent, if the adolescent is eligible. In cooperation with the involved institutions and local government, informative meetings will be scheduled to inform referrers about this study and the information folders will also be made available to referrers.

